## Abstract

Supplemental Digital Content is available in the text

## Introduction

1

A massage chair uses mechanical devices such as massage bolls, rollers, and airbags, and automatically massages the whole body.^[1]^ Depending on the development of the technology, the massage sensations elicited by experts, such as tapping, patting, finger pressure, and stretching, could be experienced with the massage chair.^[2]^ Mechanical massage with a massage chair is known to have the effect of reducing muscle strain,^[3]^ improving sleep quality,^[4]^ and recovering mental fatigue and enhancing cognition.^[1]^

If no definite evidence exists on the current or future negative psychological and social concerns associated with short stature, a previous study proposed that the idiopathic short stature should not be treated with growth hormone (grade 2C).^[5]^ This proposal assumes that the psychological and social benefits associated with an additional growth increase are less important than the cost and burden of long-term treatment.

Many alternative treatments have been developed for promoting growth because growth hormone treatment for idiopathic short stature is not recommended. One of these alternative treatments is massage therapy. The growth-promoting effect of massage was mainly reported in premature babies. Massage can lead to 5.1 g of daily weight gain,^[6]^ and is thought to be the result of increased vagal activity and gastric motility in premature babies.^[7]^ Height and thoracic circumference were significantly increased in Korean premature babies who received massage twice a day for 14 days.^[8]^ Although no weight gain was shown in premature boys after massage twice a day for 4 weeks, the quality of growth improved by reducing the adiponectin circulation and body fat accumulation.^[9]^ The massage method affects growth stimulation because the 6-week meridian massage for 15 minutes per day showed higher growth rate than general massage.^[10]^

Studies that examined the growth effects of massage at ages beyond infancy are rare. Therefore, identifying the potential of massage for promoting child growth can provide additional evidence for childhood growth alternative therapy. A recently developed massage chair (BEG-100) can strengthen the stretch around the knee after fixating the knee and ankle areas. Periodic stretching of the soft substrate is known to change substrate rigidity and develop fibrous tissue.^[11]^ Stretching by BEG-100 is expected to have a positive effect on growth.

We prepared a prospective study to investigate the effects of a massage chair on growth by comparing with national standard statistical data. The results will provide information on the potential effects of the massage chair on growth stimulation and the possible adverse events (AEs) associated with the use of the chair in children.

## Methods

2

### Ethics approval

2.1

The study will be performed in accordance with the principles of the Declaration of Helsinki and the Ethical Guideline for Clinical Research, and the institutional review board (IRB) of Kyung Hee University Korean Medicine Hospital (KOMCIRB 2019-03-002). The study protocol was registered with the Clinical Research Information Service (KCT0004673).The IRB will check the study protocol at least yearly. Any modifications of the protocol will be approved by IRB before its execution. Korean medicine doctors will explain the study to the children and their guardians and acquire written informed consent. If AEs occur during the study, appropriate medical treatment will be provided until the participant recovers. All the participants’ data will be documented by the code number and participants’ initials, and the documents will be stored in locked file cabinets with controlled access. The study results will be released to the participants, health care professionals, and public via publications.

### Study design

2.2

This is a prospective single-group study protocol that will include children aged 11 years with average height. It aims to observe the potential of a 24-week massage for growth promotion. The study protocol conforms to the Standard Protocol Items: Recommendations for Interventional Trials.

### Participants

2.3

Thirty-eight children from Kyung Hee University Medical Center will be recruited through posters and banners. The participants and their guardians will receive research information such as objectives, procedures, and potential benefits and harms through standardized dialogues. Informed consent will be acquired from the children and their guardians ahead of the screening process. The participants will be allowed to withdraw from the study at any time they want. The research procedure will be conducted as shown in Figs. 1 and 2. All the participants will undergo a massage chair treatment at home for 24 weeks. After the screening session, 4 assessment visits will be planned for the children. The guardians will receive text messages as reminders of the scheduled visits.

**Figure 1 F1:**
[figure not shown]
Schematic chart of the study process. FAS = full analysis set, GH = growth hormone, IGF-1 = insulin-like growth factor-1, IGFBP-3 = insulin-like growth factor binding protein-3, PPS = per protocol set, SAS = safety assessment set.

**Figure 2 F2:**
[figure not shown]
Schedule of enrolment, interventions, and assessments.

### Sample size

2.4

The number of participants was calculated on the basis of comparative studies that verified the effects of massage on growth because previous studies on massage intervention using a massage chair for growth promotion are rare. Thirty children per group were selected for judging the growth effect of massage in previous studies.^[12,13]^ We calculated the appropriate total number of participants to be 38 by considering the 20% dropout rate.

### Inclusion criteria

2.5

Boys and girls aged 11 years whose heights range from 145.0 to 155.0 cm (considering the size of the massage chair)Children who agree to participate in this study and have written informed consent forms signed by their representative.

### Exclusion criteria

2.6

Growth retardation from endocrinopathy (growth hormone deficiency, hypothyroidism, type 1 diabetes, and so on)History of intrauterine growth retardationDiagnosis and treatment of chronic or terminal diseases (hypertension, obesity, hyperlipidemia, diabetes, thyroid disease, cancer, and so on)Diagnosis and treatment of musculoskeletal diseases that make implementation of the massage chair difficult (congenital malformation, scoliosis, osteogenesis imperfecta, musculopathy, and so on)Clinically significant disease or history of diseases of the liver, pancreas, kidney, nervous system, respiratory system, endocrine system, cardiovascular system, urinary system, hemopathy, tumor, or psychopathy, especially a history of severe heart disease or major psychopathy such as mania/hypomania, bipolar disorder, depressive disorder, anxiety disorder, suicidal tendency, schizophrenia, attention deficit hyperactivity disorder, and autism spectrum disorderTreatments for improving height growth such as growth hormone therapy, hormone replacement therapy, medications, health functional foods, and herbal medicines within 4 weeks before the screening assessmentParticipation in another clinical study within 4 weeks before the screening assessment, or planning to participate in another clinical study during the intervention periodPlan to receive treatments for improving height growth within the research periodUnsuitability for study participation for reasons other than the aforementioned as judged by the researchersOutside the normal range of the related examination.

### Intervention

2.7

After the screening, all the appropriate participants will be assigned to the BEG-100 treatment. BEG-100 is a massage chair made by Bodyfriend, Inc.(Seoul, Republic of Korea) to promote height growth (Fig. 3). The manufacturer will deliver BEG-100 to the participants’ home after enrolment and is also responsible for the management and return of the massage chair. All the participants will sit on the chair and apply growth mode (lower body growth for 20 minutes and whole-body growth for 10 minutes) every day for 24 weeks. BEG-100 stimulates the knee growth plate by stretching the knee and lower limbs in the lower body growth mode. It stimulates the vertebral growth plate by stretching the vertebrae and upper body in the upper body growth mode. It stretches the upper and lower body in the whole-body growth mode.

**Figure 3 F3:**
[figure not shown]
Massage chair (BEG-100).

BEG-100 uses a thermal massage ball and thermal airbag for realizing the massage sensation with warm hands. The leg parts of BEG-100 are automatically adjusted to the length of the user's legs ranging from 9 to 20 cm. For the feet, 2 rollers massage the soles and 3 airbags massage the heels.

The participants should not take any other medications, Korean medicines, health functional foods, and treatments that can influence growth. Participants receiving growth-promoting medications, including growth hormone; growth-promoting Korean medicines, including herbal medication tonifying Qi, tonifying blood, or improving digestion; growth-promoting health functional foods, including nutritional supplements; growth-promoting treatments, including leg correction, orthotherapy, physical therapy, rehabilitation, acupuncture, electroacupuncture, pharmacopuncture, bee venom, moxibustion, cupping, cognitive behavioral therapy, and mind-body therapy will be excluded from the study participation.

The participants will stop conducting the intervention with the massage chair and will undergo relevant treatment if AEs associated with BEG-100 occur, such as abrasion, bruise, contusion, muscle and tendon damages, allergic symptoms, burns, and vertebral sprain or fracture. Compliance of device use in the home will be regularly monitored by filling in a self-written tabular form in every visit (Additional file 1.docx, SDC link:).

### Outcome measurements

2.8

#### Height

2.8.1

Height will be measured with the participant barefoot, and the value will be rounded off to 2 decimal places. Height will be measured by a trained nurse at the same time of day (±1 hour) to reduce height deviation during the day. Height will be measured with a portable stadiometer (Seca 213, Seca GmbH, Hamburg, Germany) that can measure heights ranging from 20 to 205 cm. Height will be measured from screening to close-out.

Height percentile and standard deviation score (SDS) will be based on the 2017 Korean growth chart.^[14]^ Values outside 3 standard deviations from the median of the height were removed to avoid biased calculation. The height percentile was smoothed by Loess regression (Proc Loess in SAS 9.4) for removing fluctuation associated with age or height. The values were converted to normal distributions by applying the Box-Cox transformation.

Growth rate will be calculated by dividing the height difference by the number of days required. The seated height-to-standing height ratio will be determined by measuring height in the seated position with Seca 213.

#### Bone age

2.8.2

On hand radiography at visits 2 and 5, bone age will be computed using the Tanner-Whitehouse (TW) method. The maturity of the hand ossification centers will be assessed as a radius-ulnar-short bone (RUS) score from 0 to 1000 as compared with the bone age chart according to sex and age.^[15]^ Two-year-old boys have a RUS score of 42, and 2-year-old girls have a RUS score of 126. The RUS score of 1000 is computed for 16.5-year-old boys and 15.0-year-old girls. The TW3 RUS score was based on the American, Argentine, Belgian, British, Italian, Japanese, and Spanish surveys between 1960 and 1995. The TW3 RUS score will be calculated by researchers who have been trained for > 3 months before assessment.

Predicted adult height will be calculated from the measured height and RUS score using the TW3 equations, which were developed according to boys, girls before menarche, and girls after menarche. The height SDS for bone age will be determined according to the 2017 Korean growth chart.

#### Weight

2.8.3

Weight will be measured in light clothing and the value will be rounded off to 2 decimal places. Weight will be measured by a trained nurse using a load cell scale (Jenix DS-103 M) that can measure weights ranging from 10 to 200 kg. Weight will be measured from screening to close-out. Body mass index (BMI) will be calculated by dividing the weight by the square of the height.

#### AEs

2.8.4

To assess overall clinical safety, the researchers will collect all voluntarily reported AEs during each visit and record the name, date, severity, course, seriousness, causality, and treatment performed for the AE in the case report form. The participants and their guardians will be asked, “Has there been any AE since the last visit?” When the child does not report any AE, the severity is considered minor or nonexistent. If the reported AEs are not sufficient for the participant to drop out from the study, the severity is considered moderate. When the child has to withdraw from the study to undergo treatment for the AE, the severity is considered severe.

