### Statistical analyses

2.9

Outcomes will be analyzed with a full analysis set (FAS) and per protocol set (PPS). The FAS targets all participants whose heights can be measured after starting the intervention and have no major violation of inclusion criteria. PPS targets all the participants who have been treated with the massage chair for >118 days (70% of the total 168 days). The safety analysis targets all participants with available safety data obtained by phone or visit.

Continuous data will be arranged as representative values such as mean and standard deviation. Height percentile, height SDS, predicted adult height, seated height-to-standing height ratio, and BMI will be tested by using the paired *t* test or Wilcoxon signed-rank test. The final height and weight will be measured by using a 1-sample *t* test or Wilcoxon signed rank-test from the parameters after 24 weeks of initial percentile. The final bone age will be tested by using a 1-sample *t* test or Wilcoxon signed rank-test, from the age after 0.5 years of the initial bone age. AEs will be described as frequency, percentage, and 95% confidence interval for the occurrence rate in all the participants. The difference in the incidence of AEs between before and after intervention will be tested by using a *χ*^2^ test or Fisher exact test. A secondary analysis will be conducted by grouping according to boys, girls before menarche, and girls after menarche. If necessary, analysis of covariance will be used.

The significance level is 0.05 for all the statistical tests, and 2-tailed tests will be performed. Missing values will be imputed using the last-observation-carried-forward method.

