### Data monitoring

2.10

The data monitoring committee is composed of three Korean medicine doctors employed in Kyung Hee University Korean Medicine Hospital but who have no participation in this study. They will conduct monthly monitoring of document reporting, protocol violation, and AEs during the study. Any interim analyses and guidelines for discontinuation will follow the standard operating procedure of the Korean Medicine Clinical Trial Center of Kyung Hee University Korean Medicine Hospital. Issues found will be discussed with the principal investigator.

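### One general question, with a child's silence graded as minor or absent, risks under-counting the minor chair-related injuries that the protocol itself expects

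*Protocol article*

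**What the plan says.** Section 2.8.4 (AEs) states that "the researchers will collect all voluntarily reported AEs during each visit". On the prompt, it says "The participants and their guardians will be asked" a single question: "Has there been any AE since the last visit". It then sets the severity scale: "When the child does not report any AE, the severity is considered minor or nonexistent". A reported event that does not lead to dropout is moderate, and one that forces withdrawal for treatment is severe. The Discussion repeats that the safety comparison uses events reported voluntarily.

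Section 2.7 (Intervention, after Figure 3) gives examples of chair-related events that lead to stopping use and to treatment: "abrasion, bruise, contusion, muscle and tendon damages, allergic symptoms, burns, and vertebral sprain or fracture".

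Section 2.9 fixes the safety summary: "AEs will be described as frequency, percentage, and 95% confidence interval for the occurrence rate in all the participants". It defines the safety population by data from telephone or visit contact and adds a test of incidence before against after the intervention. In section 2.10 the monitoring committee's task is described thus: "They will conduct monthly monitoring of document reporting, protocol violation, and AEs during the study".

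**The concern.** The growth aim is the only one stated in section 2.2, but the Introduction also promises information on possible harms, and the Discussion calls the study a pilot for later randomised trials. With no comparison group, the absolute event percentage and its interval carry most of the safety message.

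That percentage counts only what is reported. A small abrasion or bruise from daily use at home, some weeks before a visit, is easily left out of an answer to a general question. The severity scale makes this worse, because minor has no place of its own: it is assigned only when the child reports nothing, and there it is merged with no event. If such events are missed, the trial could describe the chair as gentler than it is, and a later trial would be planned on that figure.

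**Working it through.** **1. What the text fixes.** Setting sections 2.8.4, 2.7 and 2.9 side by side:

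- Elicitation is one general question, put to both child and guardian.
- The expected chair-related events are listed, but nothing shown links that list to the question.
- Silence from the child is one category covering both minor and none. Any reported event that does not end participation is moderate, however slight.
- The estimate is the percentage with an event and its 95% interval.

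So a minor event that is not mentioned adds nothing to the numerator, and the grading rule offers no way to recover it.

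**2. Number of contacts.** Section 2.3 plans four assessment visits after screening, which makes five visits. Section 2.8.2 places hand radiography at visits 2 and 5. If visit 2 is baseline (an inference, since the schedule figure is not shown), visits 3, 4 and 5 follow the start of chair use. Over 168 days that averages 168/3 = 56 days, or 8 weeks of recall per visit. Telephone contacts would shorten this, but their timing is not given.

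**3. The denominator.** The plan's own figure reproduces: 30/(1 − 0.20) = 37.5, rounded up to 38.

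**4. Possible size.** The documents give neither an expected event rate nor a reporting share, so both are assumed here. Let p be the true proportion of children with an event and s the share of those children who are counted. With no false reports, the expected reported rate is p × s. The table takes p = 20% and n = 38; coverage is the probability that the exact (Clopper-Pearson) 95% interval contains the true 20%.

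| s | Expected reported rate | Coverage of the true rate |
|---|---|---|
| 1.0 | 20% | 98% |
| 0.9 | 18% | 97% |
| 0.7 | 14% | 92% |
| 0.5 | 10% | 75% |
| 0.3 | 6% | 40% |

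With p = 10%, the chance that no child has a recorded event is (1 − 0.10)^38 = 2% if s = 1, and (1 − 0.05)^38 = 14% if s = 0.5.

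**5. A clean record.** With 0 events in 38 children, the exact two-sided 95% upper limit is 1 − 0.025^(1/38) = 9.3%. This bounds the rate of reported events. It bounds the rate of actual events only if s = 1, and it does not itself measure any bias.

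**The case against.** Several points on the other side are sound.

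- A reader might infer that events come to light only if a family volunteers them. The documents do not support that. The question is put actively to two informants, telephone data are mentioned, and section 2.7 has participants stop and receive treatment when a chair-related event occurs, without tying this to visit days. However, no telephone schedule or telephone question is described, and the committee is said to monitor events, not to seek new ones.
- A reader might also infer that the rate is shown to be biased. It is not. The direction is a reasonable inference, but the size depends wholly on assumed values. With 90% of affected children counted, the distortion is small (18% for 20%, coverage 97%).
- A general, non-leading question is a usual way to elicit adverse events and is not an error. Prompting has its own bias: active 11-year-olds have bruises and scrapes unrelated to the chair, and without a control group these cannot be subtracted. This stands, and it is why the two kinds of report must be kept apart.
- A structured prompt could sit in the case report form or the compliance form, neither of which is shown. That is possible, but the stated method, repeated in the Discussion, is voluntary report.
- In the before/after test, under-reporting may partly cancel if the same question serves both periods. It does not cancel in the absolute rate.

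None of these points answers the grading rule, which is in the text and merges minor events with none.

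**Conclusion.** The concern holds as a risk of under-counting minor events. The protocol pairs a general question with a rule that makes an unreported minor event indistinguishable from no event, while naming in advance injuries that include minor ones. The absolute event percentage and its 95% interval are therefore likely to be too low. The documents do not allow the amount to be computed: under the assumed 20% true rate it runs from negligible at 90% counted to serious at 50% or less. The downward direction assumes that some affected children are not counted and that false reports do not make up the difference.

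The documents do not support a conclusion that serious injuries would go unseen. Nor is there a contradiction between monthly committee review and less frequent visits. This is a worthwhile, inexpensive improvement to data collection plus the repair of one badly drawn severity category.

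**What to change.** 1. Keep the open question and ask it first. Then, at every visit or telephone contact where safety data are taken, ask child and guardian yes/no about each event type listed in section 2.7.
2. Record causality for every event, as section 2.8.4 already intends, and report unprompted and prompted events separately, each with its percentage and 95% interval.
3. Replace the rule that grades a child's non-report as minor or absent. Record no event and minor event as different categories, so that a slight event that is reported can be graded minor and not moderate.

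The cost is about one more page in the case report form and a few minutes per contact. The downside is that prompting will pick up everyday injuries that a single-group study cannot separate from chair-related ones. The prompted rate should therefore be presented as an upper figure beside the unprompted one. The existing text messages to guardians are visit reminders; using them to query events before each monthly committee review would need a new schedule and is not proposed. No treatment or stopping rule changes.

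### Adverse event severity is graded by reporting and withdrawal rather than intensity, so no reported event can be mild, and an undefined link to stopping the chair leaves some grades ambiguous

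*Protocol article*

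**What the plan says.** Section 2.8.4 (AEs) lists severity as one of several items for each event. Researchers are to "record the name, date, severity, course, seriousness, causality, and treatment performed for the AE in the case report form". It then defines three grades:

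- Lowest: "When the child does not report any AE, the severity is considered minor or nonexistent".
- Middle: "If the reported AEs are not sufficient for the participant to drop out from the study, the severity is considered moderate".
- Highest: "When the child has to withdraw from the study to undergo treatment for the AE, the severity is considered severe".

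Section 2.7 (Intervention) has a separate rule on use of the device: "The participants will stop conducting the intervention with the massage chair and will undergo relevant treatment if AEs associated with BEG-100 occur". The examples it gives are "abrasion, bruise, contusion, muscle and tendon damages, allergic symptoms, burns, and vertebral sprain or fracture".

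Section 2.9 (Statistical analyses) plans the safety summary: "AEs will be described as frequency, percentage, and 95% confidence interval for the occurrence rate in all the participants". It adds a test comparing AE incidence before and after the intervention. It names no summary by severity.

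**The concern.** A severity grade should say how intense an event was. These definitions mention no symptoms, functional impact or clinical findings. They record whether anything was said at the visit and whether the child left the study. Leaving can depend on things other than intensity, since section 2.3 allows participants to withdraw whenever they wish.

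The lowest grade also assigns a severity to the absence of a report, and so puts a minor event and no event in one class.

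The Introduction names possible AEs in children as one of the two things the results will inform, and the Discussion calls the study a pilot for later randomised trials. The device stretches the knees and spine of 11-year-olds at home every day for 24 weeks. A reader of the results would expect the severity field to separate trivial events from bad ones.

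**Working it through.** No arithmetic applies, and no figure in the plan bears on the point. The check is to apply the definitions literally and then set sections 2.7 and 2.8.4 side by side.

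**Step 1: section 2.8.4 alone.** The lowest grade requires that no AE was reported. Every reported AE therefore falls in one of the upper two grades, and none can be mild. This follows from the wording and needs no data. The upper two grades differ only in whether the child has to leave the study.

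**Step 2: add section 2.7.** Its rule applies to AEs associated with the chair and sets no intensity threshold. It speaks of stopping the intervention, whereas the highest grade in section 2.8.4 speaks of withdrawing from the study. The article neither equates the two nor separates them, so there are two readings.

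| Case | Reading A: stopping the chair is study withdrawal | Reading B: it is not |
|---|---|---|
| Nothing reported | lowest | lowest |
| Trivial AE unrelated to the chair, child stays | moderate | moderate |
| Abrasion from the chair, use stopped, treated, no other reason to leave | severe | moderate |
| Burn from the chair, use stopped, treated, no other reason to leave | severe | moderate |
| Vertebral fracture from the chair, child has to leave for treatment | severe | severe |

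**Step 3: what the table shows.**

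- The abrasion and the burn share a grade under each reading.
- The abrasion changes from moderate to severe between readings, although the event is the same. Two assessors could each follow the article and disagree.
- Under A, every chair-associated AE is severe, and moderate is left only for unrelated events.
- Under B, the abrasion and the fracture get different grades. If the child with the fracture stayed in the study, they would share one.

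**Step 4: effect on the stated analysis.** Section 2.9 uses counts of AEs, percentages, a 95% confidence interval for the occurrence rate, and a before-and-after comparison of incidence. None of these takes the severity grade as an input, so all are unchanged, provided that children with no report are not counted as having an AE.

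**The case against.** The best case for the plan is that little depends on this field. Section 2.9 plans no severity summary. Section 2.8.4 also records the event's name, course, seriousness, causality and treatment, so a fracture and an abrasion remain distinguishable. Section 2.10 has the monitoring committee look at AEs monthly and does not tie it to the severity grade. The study is a small single-group pilot, and the growth outcomes, sample size and significance level are untouched.

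Most of this stands, and it rules out several stronger readings that a reader might infer:

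- *That a planned severity table will be misleading.* The article plans no such table. The defect is in the recorded variable and matters wherever that variable is used.
- *That an abrasion and a vertebral fracture always share a grade.* They need not: if stopping the chair is not withdrawal, a fracture that forces the child out is severe and the abrasion is moderate.
- *That sections 2.7 and 2.8.4 contradict each other.* One concerns use of the chair after device-associated AEs, the other study withdrawal for any AE. A child could stop the chair and still attend visits. What can be shown is that their relation is undefined and that some grades depend on it.
- *That the study cannot inform a later trial or the monthly monitoring.* The other recorded items keep part of that information.

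The objection does not rescue the severity field. None of the other items is a graded intensity, and intensity not captured at the visit may be hard to reconstruct later.

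**Conclusion.** The point holds as a defect in one recorded safety variable. By construction, no reported AE can be mild, the grade reflects reporting and study disposition rather than intensity, and events of very different intensity can receive the same grade. Because the article does not say whether stopping the chair is study withdrawal, a chair-related abrasion can be graded moderate or severe.

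This is a rule the article states, not a detail left to a fuller document. The conclusion assumes that the definitions are applied as written. It does not extend to the planned occurrence rate, its confidence interval, the incidence comparison or any growth outcome.

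Priority is moderate, not a must-fix: safety in children is a stated aim, but no planned analysis uses the grade and other recorded items preserve part of the information.

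**What to change.** In section 2.8.4 and the case report form:

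- Grade each reported AE as mild, moderate or severe by its intensity, for example by interference with usual activities.
- Remove the severity grade for children who report nothing.
- Record the action taken with the chair and withdrawal from the study as two separate fields. Treatment and course are already recorded and need no change.

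Reconcile sections 2.7 and 2.8.4 by stating whether stopping the chair counts as study withdrawal. That choice is for the investigators; the point requires only that the two sections agree.

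The cost is new case report form wording and a minor amendment, with no extra visits, staff or participants. It is best done before data collection.
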